### Study population and procedures

#### Study site and populations

The study will be conducted at four craniofacial sites in Brazil including Hospital de Reabilitação de Anomalias Craniofaciais (HRAC) in Bauru (state of Sao Paulo), Hospital Santo Antônio- Centrinho: Obras Sociais Irmã Dulce in Salvador (state of Bahia), Hospital de Clínicas de Porto Alegre (HCPA) in Porto Alegre (state of Rio Grande do Sul), and Instituto Materno Infantil [name]/IMIP (IMIP) in Recife (State of Pernambuco). All of these clinics have had a long experience in providing care to patients with oral clefts.

#### Inclusion and exclusion criteria

##### Inclusion criteria

In this study, NSCL/P is defined as all cases of unilateral or bilateral clefts of the lip with or without cleft palate excluding the following: cases with recognized syndromes, cases with a chromosome abnormality, cases with one or more other major structural anomaly, cases with cognitive delay (IQ or equivalent less than 80), or cases exposed to recognized teratogens in utero (phenytoin or valproic acid). Cases with cleft palate only will not be included in the study as specified in Chapter 1. The following define the inclusion criteria for the study:

1. Women with NSCL/P, who are 16 to 45 years of age (after 45 fecundity decreases substantially) and who attend or have attended the craniofacial clinic for their care.

2. Women (age 16 to 45 years of age) who have at least one natural child of any age with NSCL/P who receives (received) care at the participating craniofacial clinics.

3. All women must reside in the catchment area of the study, which includes the state where the clinic is located and surrounding states.

##### Exclusion criteria

1. Having a first degree relative (that is a parent, sibling or child) who has cleft palate only.

2. Cases resulting from consanguineous couples (first, second, and third degree, i.e., first cousins or closer).

3. Couples where at least one of the two is definitely sterilized.

4. Women who are using intrauterine devices

5. Women who are using injectible contraceptives

6. Women on anti-epileptic drugs (The metabolism of anti-epileptic drugs requires a great deal of folic acid. Therefore, it is very difficult to verify the effect of folic acid on the prevention of clefting among these women. In order to avoid this situation, such women will not be included in this study).

7. Women on drugs that contain benzodiazepines

8. Women who are pregnant. They will be re-contacted later at an appropriate time for participation in the study.

9. Women who are planning to move outside of the catchment area of the study within the next year.

10. Women who have B12 deficiency (B12 level is below 174 pg/ml or 134.328 pmol/L).

11. Women who are allergic to folic acid.

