#### Enrollment and baseline data collection

Once screened, the Clinical Coordinator will enroll eligible subjects who provide informed consent. The Clinical Coordinator will complete the enrollment form, and will obtain a blood sample (about 8 ml) from the subject for baseline measures of RBC, hemoglobin, B12, and serum/RBC folate.

Blood samples will be analyzed at a maximum of 2 weeks. Enrollment of subjects with normal B12 levels will be confirmed. Subjects found to be B12 deficient will be referred to a hematologist for treatment, and will be excluded from participation.

The Clinical Coordinator will randomize each confirmed subject into the 0.4 and the 4 mg folic acid groups (see section 3.6) and will dispense the folic acid pillbox with the relevant pillbox ID number. Study pills will be sent to randomized subjects by mail in most cases; subjects with unreliable addresses or who frequently attend the clinic for care receive their pills at the clinic. When delivered by mail, the clinical coordinator will contact the subject by phone to confirm their receipt of the pillbox.

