#### Blood collection

Folate (Serum and RBC) levels will be assessed, at baseline (prior to supplementation), every 12 months after enrollment, and at pregnancy. B12 levels will be assessed at baseline and subsequently every year to monitor for B12 deficiency. Folate and B12 tests may be conducted at the own laboratory facilities of the clinic/hospital when available or alternatively at local laboratories determined by the Co-Principal Investigator. The Clinical Coordinator and Co- Principal Investigator will monitor B12 levels and will refer subjects with B12 deficiency to the hematology service for treatment. Randomized subjects found to be B12 deficient may be temporarily or permanently suspended from the study drug based upon recommendations of the hematology referral.

Based on clinical and research experience, few subjects (perhaps none) are expected to ask for their blood results. If requested prior to the end of the study, an independent physician serving in the clinic will provide confidential results to the subject. The subject will also have the opportunity to discuss what her results mean (in terms of being within normal range or not) with the physician independently from other study subjects and research unit staff. This procedure will prevent sharing the results with other study participants as well as with any member of the research team. Since no data is available on what these folate measurements will actually mean in terms of the levels of folic acid supplementation that are provided, it would be impossible for any single woman to interpret these data points in a way that could result in her un-blinding. Therefore, any disclosure of folate test results under these specific circumstances will not affect the blinding of study subjects or of research unit personnel.

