#### Related risks

Potential risks involved in this study include those of blood drawing and interview participation, which are felt to be minimal. Folic acid supplementation has overall three aspects that have already been discussed in the literature:

1. The use of folic acid may mask vitamin B12 deficiency in cases of pernicious anemia and cause irreversible neurological damage. In order to avoid this effect, a B12 assay on every subject will be performed prior to folic acid administration, and every year thereafter. Complete blood tests will be performed on collected samples at enrollment to help detect anemia. Current exposure to folic acid through fortification in the US has been reported not to increase the risk of masking anemia
[122]. This does not imply though that high doses of folic acid do not necessarily increase the masking risk, mainly for cases with B12-deficiency related neuropathy with no anemia. Yet due to the small percentage of subjects expected to have B12 deficiency, the assessment of B12 levels on a yearly basis after supplementation provides an appropriate strategy to monitor subject safety related to this issue. The added cost compared to added benefit of more frequent blood sampling to measure B12 (or other analytes) is considered high in terms of increasing the burden on subjects and lowering motivation that it should be avoided.

2. It has been suggested in the literature, though not confirmed, that high folic acid doses, such as the one used in the present study, may increase the risk of spontaneous abortions (expected spontaneous abortion rate = 15%). The numbers of spontaneous abortions will be reported and the Data Safety Monitoring Board (DSMB) will determine whether these exceed the threshold for an adverse event.

3. It has been suggested in the literature, though not confirmed, that folic acid increases twinning. Should a pregnancy result in twins, twin pregnancies in general have an increased risk of premature delivery with an intendant risk of increased mortality and morbidity for the infant, and also an increased risk of maternal complications including pre-eclampsia. Therefore, information on this matter will be collected, and the DSMB will evaluate whether the rate of twinning exceeds the threshold for an adverse event.

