		-Check willingness of potential subject to participate	
Screening	Directly or within a week period after introduction into study	Screen subject for eligibility	FA02
Enrollment	Directly or within a week period after screening	-Obtain informed consent	FA03
		-Obtain blood sample from subject	
		-Inform subject of process of study drug dispensing and next follow-up	
Verification of B12 and pregnancy test results, randomization, dispensing study pills, and baseline contact	Within 1–2 weeks days after enrollment	-Verify blood test results (mainly B12 levels)	FA04
		Randomize subjects who have no B12 deficiency and are not pregnant and dispense folic acid pills	
		Refer subjects who have B12 deficiency to hematology service	
Follow-up onward	Every 2 months (about 8 weeks)	-Dispense and confirm receiving folic acid pills	FA05
		-Complete follow-up visit form	
Follow-up when blood sampling is due	(Once every 12 months after enrollment.	-Schedule an in person follow-up for blood sampling	FA05
		-Dispense folic acid pills	FA16
		-Complete follow-up visit form	

**Table 5 T5:** Schedule B (Data collection after detection of menstruation delay or pregnancy)

**Task**	**Timing**	**Procedure**	**Forms**
Verification of pregnancy and measuring folate levels (if pregnant).	- Whenever delay in menstruation of 14 days or more or pregnancy are identified at either at bi-monthly follow-up or contact with subject between follow-ups	- Request that subject completes a pregnancy test within a week after detection of menstruation delay if pregnancy is not confirmed (For clinic based model, pregnancy can be tested for at study clinic).	- FA19 to document pregnancy test result
		- Schedule an in-person follow-up within a week after confirming pregnancy (if subject is not in clinic when first confirmed). An in-person follow-up in this case is only required if pregnancy occurs before the end of first year post initiation of supplementation and blood sampling is required for folate measurement.	- FA16 to document folate level
		Obtain blood samples for a folate testing (if applicable).	- FA06 (if pregnancy is confirmed)
		- If pregnancy is confirmed, calculate gestational age and advise subject as when to stop taking the study pills	
		- If subject is not pregnant, then proceed with the regular follow-up and supplementation schedule for non-pregnant subjects	

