##### Laboratory equipment

The laboratory at each hospital with which the clinic is affiliated will be used for analysis of subject blood samples if possible. These laboratories will have to be equipped with appropriate equipment to be able perform measures of folate and B12 levels. In case of inability to do B12 and folate analyses at the clinic laboratory, local laboratories will be identified and contracted to perform the analysis.

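### The B12 exclusion limit is given in two units that do not agree: 174 pg/ml is about 128 pmol/L, not 134.328 (minor)

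*Protocol article*

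**What the plan says.** The only numeric B12 limit in the protocol article is item 10 under Exclusion criteria: "Women who have B12 deficiency (B12 level is below 174 pg/ml or 134.328 pmol/L".

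The limit is applied before randomisation. Enrollment and baseline data collection says: "Subjects found to be B12 deficient will be referred to a hematologist for treatment, and will be excluded from participation". Table 4, under Schedule of data collection, gives the matching step: "Randomize subjects who have no B12 deficiency and are not pregnant and dispense folic acid pills". Neither place repeats a figure, so item 10 alone defines deficiency.

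More than one laboratory may run the assay. Blood collection states: "Folate and B12 tests may be conducted at the own laboratory facilities of the clinic/hospital when available or alternatively at local laboratories". Laboratory equipment adds that where a clinic laboratory cannot do the analysis, "local laboratories will be identified and contracted to perform the analysis". No reporting unit for B12 is given anywhere. For the companion assay, Table 7 (Secondary outcome measures) has serum and red cell folate reported in ng/ml, a mass unit.

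**The concern.** A threshold written in two units should be the same threshold to within rounding. The molar figure carries six significant digits, so it looks like a computed conversion of 174 pg/ml and not a separately chosen clinical limit. A conversion can be checked, and this one does not come out.

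What is at stake is eligibility near the limit. If one site's laboratory reported in pg/ml and another's in pmol/L, women with the same B12 level could be randomised at one site and sent to haematology at the other. Enrolling a woman who met an exclusion criterion is also a reportable item under Protocol violations, so the figure that governs should be clear.

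**Working it through.** **Inputs from the article (Exclusion criteria, item 10):** 174 pg/ml and 134.328 pmol/L.

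**Assumed input:** the molar mass of B12, which the article does not give. Base case: cyanocobalamin, 1,355.37 g/mol. Other forms are tried below.

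**Formula:** pmol/L = (pg/ml x 1000) / molar mass in g/mol.

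**Step 1: reproduce the stated figure.** 134.328 / 174 = 0.772 exactly, so the article's figure is 174 x 0.772. The implied molar mass is 1000 / 0.772 = 1,295.3 g/mol.

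**Step 2: convert with the base-case mass.** The factor is 1000 / 1,355.37 = 0.738.
- 174 x 1000 / 1,355.37 = 128.4 pmol/L.
- 134.328 / 128.38 = 1.046, so the stated molar figure is 4.6% too high, by about 6 pmol/L.
- In reverse, 134.328 x 1,355.37 / 1000 = 182.1 pg/ml.
- The band in which the two figures disagree is 174 to 182.1 pg/ml, about 8 pg/ml wide.

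**Step 3: see whether another form rescues the figure.**

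| Form assumed | Molar mass (g/mol) | 174 pg/ml in pmol/L | Stated figure too high by | 134.328 pmol/L in pg/ml |
|---|---|---|---|---|
| Cyanocobalamin | 1,355.37 | 128.4 | 4.6% | 182.1 |
| Hydroxocobalamin | 1,346.37 | 129.2 | 3.9% | 180.9 |
| Methylcobalamin | 1,344.38 | 129.4 | 3.8% | 180.6 |
| Ligand-free core | 1,329.35 | 130.9 | 2.6% | 178.6 |

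The lightest of these, the ligand-free core, brings 174 pg/ml only to 130.9 pmol/L. Adenosylcobalamin is heavier (1,579.58 g/mol) and moves further away, to 110.2 pmol/L. None gives 134.328.

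**Step 4: an example.** A woman at 178 pg/ml has 178 x 1000 / 1,355.37 = 131.3 pmol/L. She is not below 174 pg/ml, but she is below 134.328 pmol/L.

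**Step 5: direction.** Every woman below 174 pg/ml is also below 134.328 pmol/L in every row above. The molar figure therefore excludes some additional women and admits none whom the mass figure would exclude.

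**The case against.** The strongest reply is that this is an editorial slip with no shown effect. The article contains no molar mass, so the mismatch appears only with an outside constant. Nothing shows that any laboratory reported in pmol/L. The only unit evidence for the study's vitamin assays is folate in ng/ml, which points to mass units, and all four sites are in Brazil. Few women should be near the limit, since Related risks argues from "due to the small percentage of subjects expected to have B12 deficiency". The criterion acts before randomisation, and randomisation is stratified by site.

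Most of this stands and sets the grade. It does not remove the error: the constant is a physical one, it is declared as an assumption, and the conclusion holds across all the forms tried.

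Three stronger readings are tempting, and the documents do not support them.

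- **That the word 'or' excludes anyone below either figure, making the working limit about 182 pg/ml.** The phrase is ordinary notation for one limit in two units. If it did mean either figure, every site would apply the same limit and no discrepancy between sites would remain.
- **That the figure could be as much as 22% too high.** That comes from the adenosylcobalamin mass (134.328 / 110.16 = 1.22). Nothing in the article suggests that a laboratory would convert serum B12 with it.
- **That sites did apply different limits.** The article shows that several laboratories may be used. It does not show that they used different units.

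**Conclusion.** The point holds as a minor arithmetic error. The two figures in item 10 are not equivalent: the molar one is about 4.6% too high in the cyanocobalamin case and at least 2.6% too high for any form tried. It corresponds to about 182 pg/ml instead of 174.

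The consequence is confined to women between about 174 and 182 pg/ml, and arises only where a laboratory works in pmol/L. How many women that is cannot be said, because the article gives neither a B12 distribution nor a B12 reporting unit. The number is zero if all laboratories report in pg/ml, which is plausible. The slip is in the cautious direction. It does not bias the comparison of 4 mg with 0.4 mg, and no estimate, power figure or stopping boundary depends on it.

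The result rests on the assumed molar mass and on reading the two figures as one limit.

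**What to change.** Ask the sponsor's clinicians to confirm that 174 pg/ml is the intended limit, since the article does not say which figure is primary. Then word item 10 as: *B12 level below 174 pg/ml (about 128 pmol/L)*. If they intended the molar figure, the mass figure should instead be about 182 pg/ml.

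Use that single limit in the eligibility checks and laboratory value checks already described under Data editing and error resolution.

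The cost is one line of text and one constant wherever those checks hold the limit. At most, women in the narrow band near the limit change eligibility, and none do if all laboratories already report in pg/ml and 174 pg/ml is confirmed.

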#### Sampling, recruitment, and screening procedures

##### Sampling

Potential study subjects include a convenience sample of women with NSCL/P and/or mothers of at least one child with NSCL/P who currently attend or have attended in the past the study clinics for their own care or for the care of their children during the study period and who meet the inclusion criteria (age and residence) listed above. Potential subjects will be invited to participate. The majority of potential subjects (about 70%) are expected to be mothers of children with NSCL/P and the rest (30%) to be women who themselves have NSCL/P. Based on published literature and review of CL/P pedigrees at HRAC clinic in Bauru, the recurrence rates in the two subject groups of women with NSCL/P and mothers to a child with NSCL/P were estimated to be about 7 and 4 percent respectively.

While women up to 45 years of age are potentially eligible to participate, the sampling frame will be limited, when possible (e.g. when women’s age is known a priori from the clinic’s records), to women who are up to 40 years of age. The rationale for this sampling frame is that chances of pregnancy and propensities to have children decrease significantly after 40 years of age. Yet, due to potential inaccuracies in the age of women in the clinic’s records used for sampling, women who are invited to participate in the study and who are between 40 and 45 years of age will still be eligible to participate in the study on age basis in order to keep a positive environment for implementation of the study in the local community.

All potential subjects are identified from the clinics’ medical records and registries in addition to active surveillance of all patients who attend the clinics for care. The study staff will search patient records to identify potentially eligible subjects based on the primary information that are available in these records including CL/P diagnosis, women’s age, and residence. All patient charts from the past 10 years will be reviewed to identify women who themselves or their children have been treated at the clinic. Study staff will search the records of subjects who will attend the clinic to also identify potential subjects on a weekly basis. The study will be promoted to all the staff of these craniofacial clinics so that they also can assist in identifying and referring subjects to the study and will be advertised in local media.

##### Recruitment

Two models of recruitment will be applied:

1. ***Outreach model***: This model uses a field-based strategy to recruit potential subjects most of whom are no longer active patients at HRAC in Bauru. This model will be implemented by the Bauru study site, given the density of potential subjects in the proximate region who have been treated at HRAC. Field visits to conduct group recruitment meetings with potential subjects at local community facilities are the primary recruitment method in this model.

2. ***Clinic-based model*****:** This model will use the craniofacial clinics as the sites for recruitment of subjects. Recruitment will be focused primarily on potential subjects attending the clinic during the study period. Additional recruitment activities will include identifying potential subjects from the clinic registry that are not active patients. This model will be implemented at all participating craniofacial clinics, including HRAC in Bauru.

##### Introduction to study and screening

Potential subjects will be contacted to verify the age and NSCL/P, present the study, and assess their interest to participate and willingness to be screened to determine final eligibility. Subjects who show interest will be offered to undergo immediate screening to confirm their eligibility.

##### Outreach model

The study staff will search patient records in the HRAC database to identify potentially eligible subjects based upon inclusion criteria in 3.2.1. The study staff will mail letters of invitation to identified potentially eligible subjects for attendance at prescheduled recruitment meetings. These meetings will take place at public facilities (e.g. health centers, schools, churches, or other public facilities) as coordinated with local community leaders. The study staff will follow-up with phone calls to check on intent to attend these meetings. In some cases, the local network of social workers may be used to visit invited subjects and confirm their intention to attend these meetings. This is especially helpful for contact with potential subjects with incorrect contact information in the HRAC database. During the first meeting, study staff will explain the purpose of the study, the study intervention, subject responsibility (e.g. compliance with study drug, maintaining follow-up), and design of recruitment, enrollment, and follow-up procedures. The study staff will offer to answer any questions the subject may have regarding the study, and will provide the subject with a study summary brochure. The study staff will screen those interested and enroll them if eligible.

##### Clinic-based model

The Clinical Coordinator will search patient records to identify a potential subjects that meet the inclusion criteria of NSCL/P and age, and will check the appointment schedule at the clinic to see if they may visit the clinic within the next six months. Subjects scheduled to visit the clinic in the next six months will be first contacted to participate in the study during their visit to the clinic. Potential subjects unscheduled to visit the clinic in the next six months and/or who no longer attend the clinic will be contacted via invitation letters and/or phone and invited to participate.

After verifying the potential eligibility status based on age and NSCL/P, the Clinical Coordinator will individually present the study to each potential subject. This first contact may take place at the clinic or via phone, and involves explaining the purpose of the study, the study intervention, subject responsibility (e.g. compliance with study drug, maintaining follow-up), and design of recruitment, enrollment, and follow-up procedures. The Clinical Coordinator will offer to answer any questions the subject may have regarding the study, and will provide the subject with a study summary brochure.

After presenting the study to the potential subject, the Clinical Coordinator will ask her whether she might be interested in participating in the study. Subjects who show interest will be offered to undergo immediate screening to confirm their eligibility. Subjects who show interest but are hesitant to be screened and enrolled will be given more time to consider their participation.

The Clinical Coordinator will ask subjects who are unwilling to participate about their reasons for not participating and whether any accommodations could be made to help them participate. This will be done in a non-coercive manner in order to inquire about information that may help to improve the study design and procedures. No further attempt will be made to recruit subjects who remain unwilling to participate.

